## Abstract

**Objective:**

To establish the feasibility and effectiveness of a rehabilitation programme using low-cost virtual reality aimed at improving postural control in children with cerebral palsy—spastic hemiplegia. It also aims to compare the effectiveness of this programme under two delivery modalities, telerehabilitation (TR) and face-to-face (FtF).

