Low-cost virtual reality exergames are well-accepted by children and adolescents due to their ludic, motivating and engaging features, which facilitate a nearly seamless incorporation into TR [16]. However, high-level evidence of the superiority of TR using low-cost virtual reality in comparison to FtF at clinical facilities interventions is still lacking. It is noteworthy that low-cost virtual reality TR also brings the possibility to standardize rehabilitation interventions, which is a pending task in neurorehabilitation [18]. By 2022, commercially available virtual reality systems cost around $500–1000 USD. Although cheaper options exist, they require to use smartphones, which increases the final cost. For this project, low-cost virtual reality refers to a system valued $100–200 USD, which in middle to high income countries is low [19, 20] in comparison to the out-of-pocket cost for transport to physical rehabilitation facilities. There are no brand-new systems for exergaming within the referred price range, nonetheless, refurbished Wii consoles, for example, can be found for <$200 USD.

This clinical trial protocol aims to establish the feasibility and effectiveness of a rehabilitation programme using low-cost virtual reality to improve postural control in children with CP. It also aims to compare low-cost virtual reality under two delivery modalities, telerehabilitation (TR) and face-to-face (FtF, control group). We hypothesize that a rehabilitation programme using low-cost virtual reality will improve postural control in children with CP and that this programme delivered using TR will be as effective as a FtF modality. The TR programme is designed to expand the coverage of physiotherapy services for children with CP in low-resource settings and in remote areas, but also to provide access to physiotherapy during restricted mobility as in the case of recent COVID-19-related lockdowns.

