### Recruitment

Children and adolescents with congenital SHE-CP will be recruited from the Rehabilitation Institute, Talca, Chile. This is an outpatient clinic that provides rehabilitation services to patients with neurological disorders including CP children. It is noteworthy, that patients from this centre will have little or no experience using a Nintendo Wii balance board. An experienced staff of health professionals, comprised of a physician and two physical therapists, will recruit participants according to the inclusion/exclusion criteria. Screening for potential participants will continue until the calculated sample size is achieved.

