### Data collection

All measurements will be performed at the same time of the day, under the same conditions and by the same assessor at each time point. Posturographic (CoP) measures for both groups will be collected using an AMTI OR67 force platform (Watertown, MA, USA). The AMTI NetForce software (Watertown, MA, USA) will be used for the acquisition of moments and forces at 200Hz. Data will be recorded, coded, and stored on a personal computer. CoP variables will be calculated in Matlab R2012 (Mathworks Inc., Natick, MA, USA).

All primary and secondary posturographic measures will be assessed under 2 static and 4 dynamic conditions for 30 seconds each: (i) standing still with eyes open, (ii) standing still with eyes closed, voluntary sway in the mediolateral direction following a metronome set at (iii) 30Hz and (iv) 60Hz, and multidirectional sway while playing 2 different videogames that challenge (v) anterior-posterior postural control (snowboard) and (vi) medial-lateral postural control (pinguin). It is expected that all assessments, including clinical ones, will be completed within 30 minutes.

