### Data analysis

Descriptive statistics will be used to summarize the demographic and clinical characteristics in both intervention groups, and unpaired t-tests and chi-square tests will be used for comparisons. For all outcome measures, the Shapiro–Wilk and Levene tests will be used to measure the normality and homogeneity of the variance, respectively. If the assumptions of normality are met, a t-test will be employed, otherwise we will use Mann–Whitney U test to determine differences between the FtF and TR groups. Also, if the assumptions of normality are fulfilled, we will employ a repeated measures analysis of variance (RM-ANOVA), otherwise will be use Friedman’s test. Post-hoc pairwise comparisons will be used to determine the interventions effect over time for each group (FtF and TR). Cohen´s *d* will be used to report effect sizes for the CoP variables. To allow repeated measures analysis, missing data will be adjusted by 1) replacing with the non-missing average values for each variable/week, and 2) performing multiple imputations. Both methods will be used to make sure that the results were concordant. For all analyses, a *p*-value ≤0.05 will be considered statistically significant. All statistical analyses will be performed using IBM-SPSS 20.0 (SPSS Inc., Armonk, NY, USA).

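### The programme's effectiveness is an aim and hypothesis, but both arms receive it and its effect is read from within-arm change, which randomisation does not protect

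*Protocol article*

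**What the plan says.** The protocol article states two aims. The Abstract (Objective) puts the first as "To establish the feasibility and effectiveness of a rehabilitation programme using low-cost virtual reality aimed at improving postural control", and the Introduction repeats it. The matching hypothesis is that "a rehabilitation programme using low-cost virtual reality will improve postural control in children with CP". The second aim compares "two delivery modalities, telerehabilitation (TR) and face-to-face (FtF, control group". The Discussion restates both.

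The sections that decide what can be concluded are these:

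- **Interventions and Allocation.** Children are randomised 1:1 to FtF or TR, and both groups receive the same 18 sessions of the same games. The control arm is the same programme delivered by a physiotherapist.
- **Data analysis.** A t-test or Mann–Whitney test compares FtF with TR. Repeated-measures ANOVA or Friedman's test is also planned, and "Post-hoc pairwise comparisons will be used to determine the interventions effect over time for each group (FtF and TR".
- **Outcomes.** Reductions in the secondary sway measures, and favourable changes in the clinical measures, are to be read as benefit of the intervention.
- **Intervention timeline and Data collection.** There are six assessments (baseline and weeks 2, 4, 6, 8 and 10). Each has six posturography conditions, two of which record "multidirectional sway while playing 2 different videogames that challenge" balance in the anterior-posterior and medial-lateral directions (the snowboard and penguin games).

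**The concern.** Randomisation makes the arms comparable for one question only: does delivery mode matter? Whether the programme works is a different question, and no child is allocated to go without it. That aim therefore falls to before-after change, which contains any programme effect plus whatever else shifts the measurements between a first and a later test. The article nevertheless commits in advance to reading improvement as an effect of the intervention.

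At stake is the label on the result. A finding that the programme improves postural control would be an uncontrolled observation reported from a randomised trial, and the Discussion intends the results to support remote rehabilitation services for children. An analysis plan could not repair this, because no analysis creates an unexposed randomised group. Only the claim can change.

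**Working it through.** **1. Which comparison answers which aim**

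| Aim | Contrast available | Protected by randomisation? |
|---|---|---|
| TR compared with FtF | Between arms | Yes |
| Programme improves postural control | Baseline to later visits, within each arm | No |

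**2. Sources of change that the document itself supplies**

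- *Practice on the tests.* There are six assessments in ten weeks with six posturography conditions each, so 6 × 6 = 36 recordings per child.
- *Training on the test tasks.* Under Interventions, Snowboard and Penguin Slide are in both of the first two series of every session. Under Data collection, the same two games are posturography conditions. Eligibility excludes children with a Wii at home, and Recruitment expects scarcely any prior use of the board. Children therefore meet these games almost new at baseline and well practised later.
- *A weaker version of the same overlap.* The Yoga game trains quiet standing with eyes open and then closed, which resembles the two static conditions.

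**3. The plan's own figure**

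The Sample size section gives 20 per arm including 5% attrition, so 20 × 0.95 = 19 evaluable. It states no target difference, so the 20 can be neither confirmed nor refuted. Solving backwards with SD 4.974 cm², two-sided 0.05 and 80% power:

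4.974 × (1.960 + 0.842) × √(2/19) ≈ 4.52 cm².

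The present point does not depend on this figure; only n = 19 is carried forward.

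**4. Illustration: how often a within-arm test is significant when the programme does nothing**

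Assumptions, none given in the document: zero programme effect; non-specific shift c in SD units; equal variances before and after; pre-post correlation r; one two-sided paired t-test at 0.05 with n = 19.

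Formula: dz = c / √(2(1 − r)); noncentrality = dz × √19; critical t with 18 df = 2.101.

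Worked case, c = 0.3 and r = 0.7: dz = 0.3/√0.6 = 0.387; noncentrality = 0.387 × 4.359 = 1.69; probability of significance 0.36.

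| Shift c | In cm² (c × 4.974) | r = 0.5 | r = 0.7 |
|---|---|---|---|
| 0.1 | 0.50 | 7% | 8% |
| 0.2 | 0.99 | 13% | 19% |
| 0.3 | 1.49 | 24% | 36% |
| 0.5 | 2.49 | 54% | 76% |

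**5. Sensitivity**

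The article does not say whether post-hoc tests are adjusted. For shifts of 0.3 to 0.5 SD, the chance that a given contrast is significant is:

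- 8% to 49% with Bonferroni over five baseline contrasts (nominal 0.05/5 = 1%);
- 4% to 33% with Bonferroni over all 15 pairs of visits (nominal 0.05/15 = 0.33%).

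More patients do not help. Pooling both arms (n = 38) at c = 0.3 and r = 0.7 raises 36% to 64%, because a larger sample detects the non-specific shift more reliably. In the TR–FtF comparison a shift common to both arms cancels, and the error rate stays at 5%.

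**The case against.** **The authors do not rely on within-arm change alone.** The Discussion cites their earlier work as having shown FtF virtual reality to be effective, and Interventions says the programme builds on similar studies. FtF can then be seen as an active control believed to work, with TR tested against it. This is fair context, but the protocol still makes effectiveness an aim of this trial, and it gives no margin or argument that would carry the earlier result into it.

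**The numbers are hypothetical.** This is true. The shift and correlation are assumed, the planned analysis is ANOVA or Friedman with post-hoc tests rather than a single paired test, and adjustment lowers the percentages. The argument about bias needs none of these figures; they only show scale.

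**The claims are hedged.** The Abstract's conclusion speaks of what may improve, and the last Discussion section frames the study as comparative. The aim and hypothesis are not hedged in the same way. The follow-ups at weeks 8 and 10, after training stops, bear only weakly on practice versus training.

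Four stronger readings may tempt a reader, and the document does not support them:

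- *Regression to the mean.* Eligibility sets no threshold on sway or any balance test, so children are not selected for a poor baseline value.
- *Concurrent therapy.* Of the recruiting centre, Recruitment says "This is an outpatient clinic that provides rehabilitation services to patients with neurological disorders including CP children". It does not say that participants continue other treatment during the trial.
- *Inferring equal arms from two significant within-arm changes.* The plan does not do this; it tests FtF against TR directly. Whether a difference test can support a claim of being as effective is a separate matter.
- *Barring within-arm p-values, or excluding only the two game conditions from balance claims.* The first is a preference and is not needed. The second would be inconsistent, since the Yoga game also trains quiet standing.

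**Conclusion.** The point holds as a limit on what the trial may claim. Effectiveness of the programme is a stated aim and hypothesis, every randomised child receives the programme, and its effect is to be determined from change over time within arms. Following the plan yields an uncontrolled before-after claim. That follows from the design and rests on no assumed number.

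The size of the problem cannot be fixed from the document. With no programme effect, 19 children, a shift of 0.1 to 0.5 SD and correlation 0.5 to 0.7, an unadjusted within-arm test is significant about 7% to 76% of the time against a nominal 5%. Adjustment lowers these figures, and smaller shifts bring them close to nominal.

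A reader might infer that the trial can show nothing useful. That goes too far: the feasibility aim and the randomised delivery comparison are untouched, and within-arm change is informative as description.

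**What to change.** 1. Name the randomised TR–FtF contrast as the confirmatory objective.
2. Restate the effectiveness aim and hypothesis as describing change from baseline in each arm, with 95% confidence intervals, and say that the change is not attributed causally to the programme.
3. Bring the following into line: Abstract (Objective and Conclusion), the last paragraph of the Introduction, the sentences in Outcomes that read reductions as benefit, the post-hoc sentence in Data analysis, and the opening of the Discussion.
4. Report the snowboard and penguin conditions separately as performance on trained tasks, and note that the Yoga game also trains quiet standing.

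The cost is a less ambitious claim and some rewording. No arm, patient or assessment is added.

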### Sample size

Using centre-of-pressure (CoP) sway area (CoP_area_) results from earlier studies [11, 22], to achieve an 80% statistical power with an alpha level of 0.05 and considering a standard deviation of 4.974 cm^2^ (after a 6-weeks intervention), we calculated a required minimum of 20 participants in each group (FtF and TR). This sample size includes a 5% attrition, which yields a total sample size of n = 40. Sample size calculation was performed using GRANMO (Institut Municipal d’investigació Médica, Barcelona, Spain). Once the investigative work has been carried out, the sample size will be verified again, and the estimation error will be adjusted. Feasibility of this study is ensured by our previous work with similar sample size, target population, outcomes, and funding [10].

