## Discussion

The aims of this clinical trial protocol are to establish the feasibility and effectiveness of a low-cost virtual reality to improve postural control in children with CP and to compare two low-cost virtual reality delivery modalities, telerehabilitation (TR) and face-to-face (FtF). We hypothesize that low-cost virtual reality will improve postural control and that both delivery methods will be equally effective. The results of this study will help to support remote access to rehabilitation services and deliver higher, compared to standard, intensity interventions. Further, this trial will support standardization and collaboration in the field of telerehabilitation by incorporating objective measures of postural control to already existing clinical measures.

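### Mean replacement of missing values stands level with multiple imputation, and it distorts either the estimated TR–FtF difference or the type I error, depending on how the average is taken

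*Protocol article*

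**What the plan says.** All of the missing-data rule is in the Data analysis section of the protocol article. To allow the repeated-measures analysis, missing data are handled by "replacing with the non-missing average values for each variable/week, and 2) performing multiple imputations". On how the two relate, the article says only: "Both methods will be used to make sure that the results were concordant". It does not say which one carries the conclusion, or what happens if they differ.

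The comparison between arms is a difference test: "If the assumptions of normality are met, a t-test will be employed", with Mann–Whitney U otherwise, and p "≤0.05 will be considered statistically significant". Cohen's d is reported for the centre-of-pressure variables. The Introduction states the hypothesis as "this programme delivered using TR will be as effective as a FtF modality", and the Discussion repeats it as "both delivery methods will be equally effective". The Sample size section allows for 5% attrition within 20 children per arm.

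**The concern.** Replacing a gap with a group average has three faults. The filled value is counted as a measurement, so the data look less variable and more numerous than they are. It takes no account of that child's earlier visits: a child with poor sway before leaving is given average sway afterwards, which matters for the within-arm comparisons over time. And the result depends on which children are averaged, which the article leaves open. The average is indexed by variable and week only.

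At stake are the estimated difference, the effect size and the error rate of the between-arm test. Running multiple imputation alongside does not settle this. Agreement with an unsound method gives little reassurance, and disagreement leaves the choice to be made after the results are seen.

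**Working it through.** **Inputs from the article.** SD of sway area 4.974 cm² after 6 weeks, 20 children per arm, 5% attrition, alpha 0.05, 80% power (Sample size section).

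**Assumptions.** Normal data, two-sided tests, values missing completely at random, equal numbers missing per arm. The article gives no target difference, so one is needed.

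**The plan's own figure.** The attrition step fits: 19 / 0.95 = 20 per arm. Solving backwards for the difference that 19 evaluable children per arm can detect:

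δ = (1.960 + 0.842) × 4.974 × √(2/19) = 4.52 cm² two-sided.

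The one-sided value is 4.01 cm². The check uses 4.53 cm² as the true difference.

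**Reading 1: average pooled over arms.** Missing children in both arms get the same value, so with missing share m the expected difference is (1 − m) × Δ:

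| Missing per arm | Δ = 4.53 | Δ = 4.01 |
|---|---|---|
| 1 of 20 (5%) | 0.95 × 4.53 = 4.30 | 3.81 |
| 2 of 20 (10%) | 0.90 × 4.53 = 4.08 | 3.61 |
| 4 of 20 (20%) | 0.80 × 4.53 = 3.62 | 3.21 |

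Cohen's d falls by less, because the filled values also shrink the SD. The within-arm variance after filling is about [(n_obs − 1)σ² + n·m(1 − m)(Δ/2)²] / (n − 1). At 20% this is (15 × 24.74 + 20 × 0.16 × 5.13) / 19 = 20.4, so the SD is 4.52 and d = 3.62 / 4.52 = 0.80, against 4.53 / 4.974 = 0.91 with no fill. Averaged over simulated trials, d goes from 0.93 for complete cases to 0.90, 0.87 and 0.81, a loss of about 3%, 6% and 13%.

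The t-test hardly moves, because the difference and its standard error shrink nearly together. Simulated rejection rates at a true difference of 4.53:

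| Missing | Complete cases | Pooled fill |
|---|---|---|
| 5% | 77.9% | 78.0% |
| 10% | 75.9% | 75.9% |
| 20% | 70.5% | 70.6% |

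Type I error stays at about 5%. A 95% interval, if one were reported, would cover the true difference in 94.8%, 94.2% and 90.1% of trials. That loss comes from the shrunken estimate: at 20% missing the average estimated standard error (1.421) agrees with the actual spread of the estimate (1.416).

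**Reading 2: average within arm.** The expected difference stays at Δ, but the standard error is too small. The ratio of the estimated to the true standard error is √[(n_obs − 1)/(n − 1) × n_obs/n]. The test uses the critical value for 38 degrees of freedom, 2.024, when only n_obs children per arm were measured. The true type I error is therefore the two-sided tail of t, on 2·n_obs − 2 degrees of freedom, beyond 2.024 × ratio:

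| Missing | Ratio | 2.024 × ratio | df | Type I error |
|---|---|---|---|---|
| 5% | √(18/19 × 19/20) = 0.949 | 1.921 | 36 | 6.3% |
| 10% | √(17/19 × 18/20) = 0.897 | 1.817 | 34 | 7.8% |
| 20% | √(15/19 × 16/20) = 0.795 | 1.609 | 30 | 11.8% |

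Simulation gave 6.5%, 7.8% and 12.0%. Here d is inflated: 0.95, 0.98 and 1.05 against 0.93. The two readings thus bias the effect size in opposite directions.

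**The case against.** Several points on the other side are right and limit the claim.

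- **Direction.** A reader might infer that mean replacement makes a finding of equal effectiveness easier. For the test as written, it does not. Pooled filling leaves the t-test almost unchanged, and within-arm filling produces more false differences, which works against that finding. The article states no margin and no confidence interval, so a false non-inferiority rate cannot be computed from it.
- **Pooling is a reading.** The article does not say whether the average is taken across arms. The Management section has researchers analyse data without access to allocation, which fits pooling but does not establish it.
- **Size.** One child per arm is lost at the planned attrition. The article projects no 10% or 20% loss, although six assessments per child leave room for more gaps than dropout alone.
- **Who drops out.** A reader might expect more missing data in TR because no therapist is present. Nothing supports that: both arms receive telephone reminders, assessments take place where therapy is delivered, and the Discussion credits TR with less travel.
- **Condensed text.** An article may leave the choice of a primary method to a fuller document, and multiple imputation is already planned. On its own, the missing label would be a thin point. What stands is that the article does fix mean replacement as one of two methods of equal standing, and that method is unsound under either reading.

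**Conclusion.** The point holds in a limited form. Mean replacement by variable and week is a stated rule that gives a wrong answer whichever way the average is taken. Pooled, it shrinks the difference by the share missing, and Cohen's d by about two thirds of that. Within arm, it leaves the difference unbiased but raises the type I error to about 6%, 8% and 12% at 5%, 10% and 20% missing.

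At the planned 5% attrition the damage is small: a 5% shrinkage, or a type I error of a little over 6%. It becomes material towards 20%. Because the trial hopes to show that TR matches FtF, a difference estimate pulled towards zero is the unsafe error under the pooled reading. This concerns the estimate and the effect size, not the p-value.

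The proportional shrinkage and the type I error do not depend on the assumed 4.53 cm²; the absolute differences, d and the rejection rates do. All figures assume normal data, two-sided tests and values missing completely at random in equal numbers per arm.

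**What to change.** Drop mean replacement, or keep it only as a labelled sensitivity analysis that states whether the average is within arm or pooled. Make the multiple imputation already planned the primary method, done separately by arm, with baseline and earlier visits in the imputation model. State that it decides the conclusion if a sensitivity analysis disagrees. A likelihood-based mixed model on all observed visits is an acceptable alternative primary analysis and needs no imputation if data are missing at random.

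The cost is a change of wording and no new data. Intervals will be slightly wider than after mean replacement, because they will reflect the information actually collected.
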